##### Adverse effects

Recorded in each of the treatment sessions through the patient references about his status and evolution.

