### Investigations

Patients who agree to participate in the study will be cited by telephone and receive ES therapy once a week. At baseline, participants will undergo an initial assessment where data on age, date of surgery, surgical intervention technique and days of catheterization will be collected. The Oxford test (to measure the pelvic floor muscular strength), the 24-h Pad Test (in order to quantify the involuntary loss of urine), the UI questionnaire ICIQ-SF, and the SF-12 questionnaire and the specific I-QoL test (to assess their quality of life) will be evaluated at first visit.

A total of ten treatment physiotherapy sessions will be held on a weekly basis (Table 1).

**Table 1 Tab1:** Treatment sessions

SESSION 1	Collection and recording of baseline data (age, intervention date and intervention technique), Oxford measurement and tests (24-h Pad Test, ICIQ-SF, SF-12, I-QoL) Delivery of the compliance form ES (10 min at 30 Hz and 5 min at 50 Hz) Explanation of the routine for home pelvic floor exercises (10 contractions maintained and 10 fast contractions to be performed three times a day)
SESSION 2	Session protocol: Registration of possible discomfort or adverse effects perceived by the patient Review of the domiciliary exercises routine and record of compliance ES (10 min at 30 Hz and 5 min at 50 Hz)
SESSION 3–5	Session protocol (as described in session 2)
SESSION 6	Collection of 24-h Pad Test data Oxford measurement Record of patient satisfaction with the treatment Session protocol (as described in session 2)
SESSION 7–9	Session protocol (as described in session 2)
SESSION 10	Session protocol (as described in session 2) Oxford measurement Collection of 24-h Pad Test data and completion of ICIQ-SF, SF-12 and I-QoL tests Record of patient satisfaction with the treatment
SESSION 11 (6 months after the end of treatment)	Collection of the 24-h Pad Test, compliance and satisfaction data

According to the allocation group, the ES technique will be applied using the Neurotrac Pelvitone® muscular electrostimulator, together with two round surface electrodes of 32 mm or an Analys Plus® anal stimulation probe of 140 mm.

In both groups, participants will be placed comfortably in a supine position with a pillow under their heads, without pants or underwear, and with the legs bent over two leg supports.

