#### *Description of the treatment session* (same for both groups)

15 min of perineal ES (with surface electrodes or intra-anal probe according to the allocation to IG or CG, respectively), composed of 10 min of direct current at 30 Hz frequency and a pulse width of 250 microseconds, to train the tonic fibres, and 5 min of alternating current at 50 Hz frequency and a pulse width of 250 microseconds, to train the phasic fibres.

Additionally, Kegel active exercises are going to be performed under the supervision and correction of the physiotherapist in each of the treatment sessions and also carried out at home. This regimen will consist of ten slow and maintained contractions of the perineal musculature (8–10 s) and ten fast contractions (3 s) to be done three times a day (twice in a supine position and once in a sitting or standing position) during the ten weeks the whole treatment lasts.

In each session, treatment adherence and possible adverse effects of the therapy will be identified and recorded in a database designed for the project.

The same treatment protocol will be followed in all sessions. In the sixth session the results of a second 24-h Pad test will be registered, the Oxford test delivered and the satisfaction with the treatment of each patient recorded. In the tenth session, the same tests as in the first session will be re-evaluated.

The indications for the 24-h Pad test will be given in the session previous to the scheduled for the patient to do it at home and bring the results on the following treatment session, excepting for that of session 1 that will be delivered at the time of acceptance in the study.

Six months after the end of the treatment, patients will be contacted by telephone for a final assessment with the purpose of checking whether the possible benefits of the therapy persist.

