##### Satisfaction of the participants with the treatment

Registered in the sixth and tenth sessions with a scale from 1 to 10 (being 1, not satisfied and 10, very satisfied).

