### Schedule

**Table Taba:** 

	Recruitment	Session 1	Sessions 2–5	Session 6	Sessions 7–9	Session 10	6 months post treatment
*Recruitment*							
Selection screening	*X*						
Informed consent	*X*						
Collection of baseline data		*X*					
*Interventions*							
Intervention CG	*X*	*X*	*X*	*X*	*X*	*X*	*X*
Intervention IG	*X*	*X*	*X*	*X*	*X*	*X*	*X*
*Evaluations*							
24-h Pad Test		*X*		*X*		*X*	*X*
Oxford		*X*		*X*		*X*	
ICIQ-SF		*X*				*X*	
SF-12		*X*				*X*	
I-QoL		*X*				*X*	
Compliance form		*X*	*X*	*X*	*X*	*X*	*X*
Recording of adverse effects			*X*	*X*	*X*	*X*	*X*
Treatment satisfaction						*X*	*X*

The different achedule phases are shown in italics

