### Sample size

To estimate the sample size, we use the randomisation and online databases for clinical trials program of the online computer software Sealed Envelope Ltd. 2001–2015 (https://www.sealedenvelope.com/power/continuous-equivalence/).

For this estimate, alpha values of 5% and beta of 20% (power of 80%) were taken into account. Based on data published in the literature [10, 12], and considering an expected difference in the 24-h Pad Test between the two studied groups of 22 g, 32 patients are needed in each arm of the study. The interpretation is as follows: “if there is truly no difference between the control (ES by intra-anal probe) and intervention (ES by surface electrodes) treatment, then 64 patients are required to be 80% sure that the limits of a two-sided 90% confidence interval will exclude a difference in means of more than 22 g".

Assuming that there could be losses to follow-up, the number of individuals to be recruited will be increased by 10% until reaching 70 patients (35 patients per group).

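### Adverse effects and satisfaction are scheduled in a way that misses men who stop early, and the article contradicts itself on the one later contact that could capture them

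*Protocol article*

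**What the plan says.** Adverse effects and satisfaction are both listed as secondary outcomes in the protocol article. Their timing is given in several places.

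**Adverse effects**
- Outcome definition (Adverse effects): "Recorded in each of the treatment sessions through the patient references about his status and evolution".
- Description of the treatment session: "In each session, treatment adherence and possible adverse effects of the therapy will be identified and recorded in a database designed for the project".
- Investigations, Table 1: the entry "Registration of possible discomfort or adverse effects perceived by the patient" belongs to the session protocol that begins at session 2. Session 1 and session 11 (6 months) have no such entry.
- Schedule table: the row "Recording of adverse effects" is blank at session 1. It is marked from session 2 to session 10 and again at 6 months.

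**Satisfaction**
- Outcome definition: "Registered in the sixth and tenth sessions with a scale from 1 to 10".
- Table 1: sessions 6 and 10, and session 11 through "Collection of the 24-h Pad Test, compliance and satisfaction data".
- Schedule table: the row "Treatment satisfaction" is marked at session 10 and at 6 months, and is blank at session 6.

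The session description says the 6-month contact is made by telephone. It gives the purpose as seeing whether any benefit has lasted. Sample size allows 10% for losses, which takes 32 per arm to 35.

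**The concern.** Comfort is part of the case for the surface technique. The Background says the intra-anal route may be unpleasant for the patient, and the Discussion says a surface technique shown to be equivalent would be the more comfortable one. Adverse effects and satisfaction are the declared outcomes closest to that argument.

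Both depend, during treatment, on the man coming back. Someone who finds the stimulation unpleasant and does not return is the person whose experience matters most for this comparison, and he is the least likely to be recorded. If such men are more frequent in one arm, that arm's adverse-effect and satisfaction figures will look better than they should, and two techniques that differ in tolerability may look alike.

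**Working it through.** No figure in the plan is in dispute here. The check is a comparison of the stated timings, followed by an illustration of size.

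**Step 1. Timings side by side**

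| Source | Adverse effects, session 1 | Adverse effects, sessions 2–10 | Adverse effects, 6 months | Satisfaction, session 6 | Satisfaction, session 10 | Satisfaction, 6 months |
|---|---|---|---|---|---|---|
| Outcome definition | yes (each treatment session) | yes | no | yes | yes | no |
| Session description | yes (each session) | yes | not mentioned | yes | not mentioned | not mentioned |
| Table 1 | no | yes | no | yes | yes | yes |
| Schedule table | no | yes | yes | no | yes | yes |

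Three columns conflict on adverse effects or satisfaction at the points that matter for early leavers: adverse effects at session 1, adverse effects at 6 months, and satisfaction at 6 months. Satisfaction at session 6 conflicts as well.

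**Step 2. What a man who stops early contributes**
- Stops after session 1: under both tables he has no scheduled treatment-phase adverse-effect record.
- Stops before session 6: he has no treatment-phase satisfaction score under any of the sources. Under the Schedule table the same is true of anyone who stops before session 10.
- Later capture: only the 6-month telephone contact. The article does not say whether men who stopped are included.

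**Step 3. Delay if he is called.** Ten weekly sessions put session 10 nine weeks after session 1, or about two months. If the call is timed from the planned end of treatment, a man who left after session 1 is asked about it roughly 2 + 6 = 8 months later. If it is timed from his own last session, the delay is 6 months.

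**Step 4. Size, on assumed rates.** The article gives no adverse-effect rates, so these are assumptions: true discomfort p₁ in the probe arm and p₂ = 10% in the surface arm, with all 35 men per arm as denominator. If a share s of affected men goes unrecorded, then
- with the same share lost in both arms, the observed difference is (p₁ − p₂)(1 − s);
- with loss in the probe arm only, it is p₁(1 − s) − p₂.

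| s | p₁ = 30%, both arms | p₁ = 30%, probe only | p₁ = 20%, both arms | p₁ = 20%, probe only |
|---|---|---|---|---|
| 0 | 20 | 20 | 10 | 10 |
| 25% | 15 | 12.5 | 7.5 | 5 |
| 50% | 10 | 5 | 5 | 0 |
| 75% | 5 | −2.5 | 2.5 | −5 |
| 100% | 0 | −10 | 0 | −10 |

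(Differences in percentage points.) Equal proportional loss shrinks the difference but never reverses it. With one-sided loss the sign changes once s exceeds 1 − p₂/p₁, which is two thirds at 30% v 10% and one half at 20% v 10%.

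**Step 5. Size against the plan's own loss allowance.** The allowance is 35 − 32 = 3 men per arm. If all three in the probe arm left because of discomfort and none was recorded, that arm's rate would fall by 3/35 = 8.6 points. At 30% v 10% (10.5 and 3.5 men expected) the observed difference would be 7.5/35 − 10% = 11.4 points instead of 20. At 20% v 10% (7 and 3.5 men) it would be 4/35 − 10% = 1.4 points instead of 10. Neither reverses, but the second nearly disappears.

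**The case against.** The strongest reply is that the 6-month contact already covers this. It is made by telephone, so attendance is not needed, and the Schedule table marks both outcomes there. A reader might infer from the outcome definitions that these outcomes exist only at attended sessions and that a man who stops leaves no record at all. The documents do not support that: the Schedule provides for both at 6 months and Table 1 for satisfaction. What remains is that the adverse-effect part of this safeguard appears in one table only, that the stated purpose of the call is persistence of benefit, that inclusion of early leavers is unstated, and that the recall period is long.

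A reader might also take the order of items in Table 1 as a timed sequence, so that each stimulation is asked about only at the next visit. That goes too far. Table 1 is a summary: its session protocol omits the supervised exercises described in the text, and the position of the assessments changes between sessions 6 and 10. Discomfort could be noted during the session in which it occurs. The gap at session 1 rests on the blank entries, not on list order.

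A third tempting reading is that the comparison will favour the less tolerable arm. That is conditional. The Background says only that the intra-anal route may be unpleasant, and Step 4 shows that attenuation is the ordinary result.

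Finally, this is a condensed article, and handling of missed visits may be set out in the full protocol. That is fair, and the absence of such a procedure here is not the finding. The finding is that the timings the article does fix conflict with one another and, as they stand, pass over early leavers.

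**Conclusion.** The point holds in a limited form. Within the ten weeks, both tables schedule adverse effects only from session 2, and satisfaction is scheduled at session 6, session 10 or both. A man who stops after session 1 has no scheduled treatment-phase adverse-effect record, and one who stops before session 6 has no treatment-phase satisfaction score. The later contact that might make this good is described inconsistently and comes six to eight months after the event.

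If intolerance drives early stopping, harm is under-recorded and any difference between arms is reduced. At the plan's own allowance of three losses per arm, the most that one arm's adverse-effect rate could fall is 8.6 points. That assumes every loss is due to discomfort and none is captured elsewhere; the allowance is a planning figure, not a ceiling. Reversal needs heavy loss confined largely to one arm.

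The equivalence conclusion on the 24-h Pad Test does not depend on this. What is at stake is the tolerability comparison. The change is worth making because it is cheap, but it does not threaten the trial's main result.

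**What to change.** 1. Reconcile Table 1, the session description, the two outcome definitions and the Schedule table. State whether adverse effects are recorded at session 1 and at 6 months, and whether satisfaction is recorded at session 6 and at 6 months.
2. State that any man who stops early, or misses sessions without rescheduling, is telephoned soon afterwards to record adverse effects since his last stimulation, his reason for stopping and the 1–10 satisfaction score.
3. State that men who stopped are included in the 6-month call.
4. Report adverse effects, and discontinuations for discomfort, by arm among all men stimulated at least once. If the full protocol or the SAP already provides for this, a cross-reference is enough.

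The cost is a short text amendment and a few extra calls. At the planned 10% loss that is about 6 men (70 − 64), by a team that already telephones patients. No visit is added.

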##### Adherence to treatment

Assessed in each of the treatment sessions, collected through a compliance form designed for the project.

##### Satisfaction of the participants with the treatment

Registered in the sixth and tenth sessions with a scale from 1 to 10 (being 1, not satisfied and 10, very satisfied).

### Schedule

**Table Taba:** 

	Recruitment	Session 1	Sessions 2–5	Session 6	Sessions 7–9	Session 10	6 months post treatment
*Recruitment*							
Selection screening	*X*						
Informed consent	*X*						
Collection of baseline data		*X*					
*Interventions*							
Intervention CG	*X*	*X*	*X*	*X*	*X*	*X*	*X*
Intervention IG	*X*	*X*	*X*	*X*	*X*	*X*	*X*
*Evaluations*							
24-h Pad Test		*X*		*X*		*X*	*X*
Oxford		*X*		*X*		*X*	
ICIQ-SF		*X*				*X*	
SF-12		*X*				*X*	
I-QoL		*X*				*X*	
Compliance form		*X*	*X*	*X*	*X*	*X*	*X*
Recording of adverse effects			*X*	*X*	*X*	*X*	*X*
Treatment satisfaction						*X*	*X*

The different achedule phases are shown in italics

### Sample size

To estimate the sample size, we use the randomisation and online databases for clinical trials program of the online computer software Sealed Envelope Ltd. 2001–2015 (https://www.sealedenvelope.com/power/continuous-equivalence/).

For this estimate, alpha values of 5% and beta of 20% (power of 80%) were taken into account. Based on data published in the literature [10, 12], and considering an expected difference in the 24-h Pad Test between the two studied groups of 22 g, 32 patients are needed in each arm of the study. The interpretation is as follows: “if there is truly no difference between the control (ES by intra-anal probe) and intervention (ES by surface electrodes) treatment, then 64 patients are required to be 80% sure that the limits of a two-sided 90% confidence interval will exclude a difference in means of more than 22 g".

Assuming that there could be losses to follow-up, the number of individuals to be recruited will be increased by 10% until reaching 70 patients (35 patients per group).

### Selection of the sample

The selection of the sample will be done by sampling of consecutive cases, from RAPbarcelona clinic and Institut Médic Tecnológic in Barcelona. In urologists or physiotherapists appointments, patients who underwent radical prostatectomy and presented with UI will be referred to the principal investigator. The protocol will be clearly explained to each of the interested patients who meet all the selection criteria and he will be asked to sign the informed consent if accept participation. After the signature the patient will be allocated to one of the two study groups.

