#### Primary outcome

##### Magnitude of urinary incontinence

According to the grams of urine collected in a pad with the 24-h Pad Test. This is a quantitative variable (expressed in grams) evaluated in the first, sixth, tenth and eleventh sessions of the study. The Pad test consists of weighing a clean pad in grams (by the same patient), then placing it and weighing it again after an established time (24 h). In case of needing an extra pad before the 24 h are completed, the procedure would be repeated until 24 h were reached. The increase in weight tells us about the severity of incontinence. The values for mild UI are from 1.3 to 20 g, moderate from 21 to 74 g and severe 75 g or more [13, 14].

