### Random allocation of groups

A consecutive inclusion will be done until the desired sample size is reached. The generation of the random sequence will be carried out by the principal investigator using the statistical software Epidat. The randomization list will be delivered to the clinics reception desk and patients will be allocated by telephone at a 1:1 ratio (assignment by third parties).

Each participant will be assigned an identification number created for the study and linked to his treatment group. This number will allow the patient for beginning the treatment sessions. Two physiotherapists previously trained for the application of the study protocol will be in charge of the sessions.

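### Allocation comes before the self-weighed baseline pad test and the baseline questionnaires, and nothing withholds the arm until these are recorded

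*Protocol article*

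**What the plan says.** All references are to the protocol article.

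- **Allocation.** Selection of the sample: "After the signature the patient will be allocated to one of the two study groups". Random allocation of groups adds that "patients will be allocated by telephone at a 1:1 ratio (assignment by third parties", from a list held at the reception desk. Each participant gets an identification number tied to his group, and "This number will allow the patient for beginning the treatment sessions".
- **Baseline.** Table 1 (Investigations) puts under session 1: "Collection and recording of baseline data (age, intervention date and intervention technique), Oxford measurement and tests (24-h Pad Test, ICIQ-SF, SF-12, I-QoL". The Schedule table agrees: consent is in the recruitment column and all five measures first appear in the session 1 column.
- **Baseline pad test.** Pad-test instructions are normally given one session ahead, so that the patient does the test at home and brings the result, "excepting for that of session 1 that will be delivered at the time of acceptance in the study". Under Primary outcome, the test starts with "weighing a clean pad in grams (by the same patient".
- **Blinding and data collection.** Study design names only the investigator doing the statistical analyses as blinded. Collection, management and data analysis has the treating physiotherapists collect the data.
- **Use of baseline.** The abstract describes the outcomes as changes. Sample size speaks of a difference in means. The analysis section plans differences with 90% confidence intervals plus adjusted differences, and names no covariates.

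**The concern.** Randomisation makes the arms comparable on what is measured before the arm is known. A self-weighed or self-reported value taken afterwards loses that protection. The Background section itself says that intra-cavitary application may be uncomfortable or annoying, so men could plausibly react differently to the two allocations. That reaction could show in how they weigh pads or answer questionnaires before session 1. The Oxford score is rated by staff, and no text says that the rater is unaware of the arm.

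Two things are at stake:

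- A distorted baseline can carry into change scores and baseline-adjusted differences. In an equivalence trial this can hide true equivalence or, more seriously, produce false equivalence.
- A man who withdraws between allocation and session 1 belongs to the intention-to-treat set with no baseline value.

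**Working it through.** **Step 1: order of events.**

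| Step | When | Section |
|---|---|---|
| Consent | Recruitment | Schedule |
| Allocation | After the consent signature | Selection of the sample |
| Group-linked number | Before sessions begin | Random allocation of groups |
| Pad-test instructions | At acceptance | Description of the treatment session |
| Baseline pad weighing | At home, result brought to session 1 | Description of the treatment session; Primary outcome |
| ICIQ-SF, SF-12, I-QoL, Oxford | Session 1 | Table 1; Schedule |

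No section places one of these measures before allocation. No section says when the patient or the physiotherapist learns the arm.

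**Step 2: inputs for an illustration.** From Sample size: margin 22 g, 32 per arm, 90% confidence interval (z = 1.645 per side), power 80%. No SD is stated, so the plan's 32 cannot be reproduced from its own inputs. Using n = 2 × [SD × (1.645 + 1.282) / 22]²:

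- SD 30 g gives 2 × (30 × 2.926 / 22)² = 31.8, which rounds up to 32.
- Any SD from about 29.6 to 30.1 g gives 32.

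SD 30 g is therefore an assumption that fits the stated size. It is also taken as the SD of the analysed change.

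**Step 3: how a baseline error enters.** Let b be a spurious between-arm baseline difference. In an unadjusted change-score comparison it shifts the estimate by b if it is absent at follow-up. If a fraction r of it recurs at follow-up, the shift is b × (1 − r). In an analysis of covariance on baseline, the shift is the regression slope times b. In a raw comparison of follow-up values, the shift through baseline is zero.

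**Step 4: size, change-score case with r = 0.** The standard error is 30 × √(2/32) = 7.5 g.

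- Chance of concluding equivalence for equal treatments ≈ Φ[(22 − b)/7.5 − 1.645] + Φ[(22 + b)/7.5 − 1.645] − 1. For b = 5: Φ(0.622) + Φ(1.955) − 1 = 0.71.
- Chance of false equivalence at a true difference of 22 g, with bias toward zero ≈ Φ[b/7.5 − 1.645]. For b = 5: Φ(−0.978) = 0.16.

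| b (assumed) | Equivalence concluded, equal treatments: normal / t-based simulation | False equivalence at 22 g: normal / t-based simulation |
|---|---|---|
| 0 g | 80% / 79% | 5% / 5% |
| 5 g | 71% / 70% | 16% / 16% |
| 10 g | 48% / 47% | 38% / 37% |

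A shift of 5 g is 5/22 = 23% of the margin. The documents give no value for b.

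**The case against.** The strongest reply is that knowledge of the arm before baseline is inferred. The article does not put allocation at the same visit as consent. Assignment is made by third parties, the schedule has no allocation row, and Table 1 lists the tests before electrostimulation within session 1. A patient might therefore complete the questionnaires without knowing his technique. This stands: the text supports a risk, not a demonstrated bias. The listing order in Table 1 does not by itself protect a pad test already done at home.

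Some stronger readings are tempting but go beyond the documents:

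- **That every baseline value is at risk.** Age, surgery date, surgical technique and days of catheterisation cannot move with allocation. Only reported or rated measures can, and Oxford is not among the listed outcomes.
- **That the error necessarily enters the primary result.** Only the abstract speaks of changes, and the covariates for the adjusted differences are not named. A raw follow-up comparison would escape.
- **That the shift passes through in full.** The same patient weighs his pads at every assessment, so a stable reporting tendency would partly or fully cancel in a change score.
- **That early withdrawal is expected.** Nothing in the article suggests it. A man who left before session 1 would also have no follow-up, so his missing baseline is not the main problem for the intention-to-treat analysis.

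**Conclusion.** The point holds in a limited form. The order of consent, allocation and then baseline is documented. Nothing withholds the arm until the self-weighed pad test, ICIQ-SF, SF-12, I-QoL and Oxford score are recorded, so these values can be influenced if the arm is already known. The effect on the efficacy comparison depends on using changes from baseline or baseline adjustment.

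The percentages under working illustrate sensitivity and do not estimate a bias. They rest on an assumed SD of 30 g, assumed shifts of 5 g and 10 g, no recurrence at follow-up and an unadjusted change-score analysis. No later analysis can restore a baseline taken before allocation, and the remedy is nearly free, so the change is worth making.

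**What to change.** Two edits are needed together.

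1. **Selection of the sample.** Change the time of allocation from after the consent signature to: *After all baseline measurements of session 1 have been recorded.*
2. **Random allocation of groups.** Issue at consent a study number that is not linked to the arm. The reception desk releases the arm by telephone at session 1, after baseline entry and before the first electrostimulation. Without this edit, the section would still require a group-linked number before sessions can begin and would contradict the first edit.

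Men who leave before session 1 would then never be randomised. Visits, measures and sample size stay as they are. The small cost is that both types of equipment must be ready at session 1. The change does not address the follow-up pad tests, which the patient still weighs himself without blinding.
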